### Ethical Considerations

The study will be performed in accordance with the recommendations for guiding physicians in biomedical research involving human patients by the 18^th^ World Medical Assembly, Helsinki, Finland, 1964. There are no perceived risks with respect to carbohydrate loading, protein solution, and immunomodulation solution as they are unlikely to interfere with cancer. The supplements being used are classified as food products, and as a result, there are no requirements in the Health Canada Food and Drug Regulations for this study. The Hamilton Integrated Research Ethics Board has approved the study protocol and documents prior to initiation. Written informed consent will be obtained from all patients prior to enrollment in compliance with International Conference of Harmonization and Good Clinical Practice guidelines and the REB.

## Results

### Primary Outcome

The primary outcome for each eligible patient will be defined as being randomized to intervention or placebo. The primary feasibility outcome will be one of the following: (1) stop, main study not feasible: estimated proportion of randomized patients <40.0% (40/100); (2) continue with protocol modifications: estimated proportion of randomized patients between 40.0% (40/100) and 59.0% (59/100); or (3) continue without modification: estimated proportion of randomized patients ≥60.0% (60/100).

### Secondary Outcomes

The secondary outcomes of the study will be defined as follows:

Compliance: intake of at least 70% (41/58) sachets of study intervention volume.Overall complications: occurrence of any postoperative complication (major or minor) from surgery following each patient’s hospital stay and up to 90 days from the initial operation. Occurrence of any postoperative infections will also be calculated.CCI at 90 days from the index surgery will be determined for each patient. This index can be calculated for each patient using the CCI Web-based calculator [26,30] following the grading of each postoperative complication according to the Clavien-Dindo classification [31].QoL: The global health-related QoL at baseline, 1 month, and 3 months following randomization will be measured using the European Organization for Research and Treatment of Cancer Quality of life Questionnaire [32,33] instrument and the Functional Assessment of Cancer Therapy-General scale [34].Length of hospital stay will be determined for each patient.

Compliance with the intervention is a secondary objective and will be taken into consideration for the success of its feasibility, as modifications to the protocol may be needed if compliance is poor. Compliance will be measured as the percentage volume of prescribed study intervention consumed, which will be measured by a patient diary in the preoperative period and nurses’ charts in the postoperative period. Postoperative complications (major or minor) will be determined following each patient’s hospital stay and up to 90 days from the initial operation. This is classified according to Clavien-Dindo classification [26,31,35].

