### Blinding

This is a double-blinded study design. All research personnel and study participants will be blinded throughout the trial. To ensure all investigators and research personnel remain blinded, the company producing the nutritional supplements and placebo will be responsible for providing the Pharmacy Research Support Services (PReSS) and information technology (IT) technician with the allocation information specific to each lot number. All prepackaged kits for preoperative intake and postoperative intake will be sent directly to PReSS. The kits received by PReSS will include a lot number that will correspond to either the intervention or placebo; however, as mentioned above, the only personnel aware of the lot numbers and associated randomization allocation will be the independent pharmacy lead, pharmacy technicians at PReSS, and the independent IT technician responsible for the randomization sequence. To ensure all research personnel remain blinded to the patients’ allocation, PReSS will remove the lot number from each kit. PReSS will also be responsible for the accountability of the supplements throughout the study.

After entering the patient information into the Interactive Registration and Randomization System, PReSS will be responsible for dispensing the appropriate kit number and ensuring the lot number has been blinded from the patient and the research personnel. The individual packets within the kits will be labeled from “30 days before surgery” to “5 days after surgery.”

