#### Immunomodulation-Formulated Liquid Diet (INergy-FLD)

In preparation for surgery, patients will consume an immune-modulating formula containing various ingredients, including arginine, protein isolate, omega-6 fatty acids, and RNA, aimed to attenuate excessive inflammatory responses without being immunosuppressive and to replenish nutrients that are depleted in a state of stress (ie, surgery), thereby enhancing the recovery process [1]. The volume of this solution is 250 mL per dose (51 g of powder reconstituted in 250 mL of cold water). Patients will be asked to consume 3 doses per day for 5 days prior to surgery and 5 days following surgery.

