### Administration

Following randomization, patients will receive blinded packages of either the intervention or the placebo, which will be administered by the PReSS, located in the A4 wing at JHCC. The patients will be responsible for administering their own supplements while at home.

Patients will be asked to consume 1 serving of 20 g of protein isolate powder mixed in 250 mL of liquid or soft foods every day from the date of randomization to up to 6 days before surgery. Additionally, they will be asked to consume 3 servings of 51 g of an immune-modulating formula mixed in 250 mL of cold water for 5 days before and after surgery as well as 2 servings of 55 g of carbohydrate-rich powder mixed in 400 mL of cold water the evening before surgery and 1 serving 2-3 hours before anesthesia. Administration of the carbohydrate loading substance will be modified for patients following the Enhanced Recovery After Surgery (ERAS) Protocol. All study participants who are also taking part in the ERAS Protocol will be asked not to take the carbohydrate loading supplement as per the ERAS Protocol and will be asked to take the carbohydrate loading substance (or placebo) provided for this study. Routinely at our center, patients undergoing colorectal surgery are enrolled in an ERAS Protocol that encourages drinking fluids on postoperative day 1. Patients undergoing hepatobiliary surgery (either pancreas or liver surgery) are not included in an ERAS pathway; however, they are also encouraged to start a diet usually composed of liquids on day 1 after surgery. Patients undergoing gastric surgery are kept nothing per mouth for 7 days. However, they are started on tube feeds on day 1 after surgery.

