At this point, patients will fill out a daily compliance diary from the date of randomization until up to 5 days after surgery. This compliance diary will be transcribed into a preoperative compliance case report form (CRF) that includes the number of packets the patient took every day, the volume that was ingested, the days it was ingested for, and the reasons patients were not compliant. While in the hospital, the nurses will be responsible for administration, as PReSS will facilitate the administration of the supplements (INergy-FLD) by adding them to the nursing care pathway of the patients. Compliance during this time will be obtained from the nurses’ log, which includes the amount of solution the patient ingested during each administration and the days the patient ingested the solution. If for some reason, the patients are unable to tolerate an oral diet (postoperative complications such as delayed gastric emptying, ileus or bowel obstruction, etc), the nurse will contact the principal investigator of the study and the order to suspend the administration of the solution will be assessed for each patient. This will be noted in the nurses’ chart and transcribed to the postoperative compliance CRF. Patients will continue to be part of the study.

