### Data Management

In addition to physical examination and QoL data, a research assistant will gather postoperative complication data from patients’ charts or electronic medical records and transcribe it on to CRFs, which will be updated daily while the patient is in the hospital. Before surgery, a compliance diary will be provided to patients to evaluate their adherence. Compliance data will also be collected from the nurses’ charts while the patient is in the hospital, with a specific CRF designed to record the volume of the supplement the patient has taken after surgery. The feasibility CRF will include reasons for two different processes: (1) reasons for not consenting and (2) reasons for not randomizing if the patient consented. Data will be stored in a secured electronic database at OCOG.

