### Statistical Analysis

Patient baseline characteristics and demographics by treatment group will be presented using descriptive statistics. The proportion of eligible patients randomized and its corresponding 95% CI will be calculated using the Wilson method. The criterion for success of this study is defined as the proportion of eligible patients randomized as ≥60.0% (60/100). If the estimated proportion is <40.0% (40/100), the trial will be considered not feasible. If the proportion is between 40.0% (40/100) and 59.0% (59/100), the trial will be considered feasible, with modifications to improve enrollment.

The difference in the proportions of any postoperative complication between groups and its corresponding 95% CI will be calculated using the Wilson method. The proportion of patients who are compliant with study therapy and 95% CI will also be calculated. Differences in compliance between treatment groups will be described. Good compliance will be defined as consumption of ≥70% (at least 41/58) sachets of the study intervention before and after surgery. If the compliance is ≥70% (at least 41/58 sachets), there will be no exploratory analysis to evaluate the reasons for noncompliance. Compliance of <70% (40/58 sachets or less) will be considered poor, and reasons for noncompliance will be further explored (eg, problems with the distribution or administration of the supplements, bad taste, side effects, inability to tolerate oral intake, etc) These reasons will be clearly stated in the compliance CRFs.

The mean (SD) of the CCI at 90 days from the index surgery will be estimated for each group, and the mean difference between groups will be estimated with its corresponding 95% CI. QoL scores will be summarized using means and corresponding SDs. The mean difference in the QoL scores between groups at 1 and 3 months will be estimated using linear models adjusting for baseline QoL scores.

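### Preoperative compliance, the larger part of the 41/58 measure, rests only on the patient's unverified diary, although the pharmacy service already holds supplement accountability

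*Protocol article*

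**What the plan says.** Compliance is the first secondary objective in the Introduction. Under Statistical Analysis the cut is fixed: "Good compliance will be defined as consumption of ≥70% (at least 41/58) sachets of the study intervention before and after surgery". Under Secondary Outcomes it is a percentage of prescribed volume, "which will be measured by a patient diary in the preoperative period", with nurses' charts as the source after surgery.

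Two other sections name the same preoperative source. Data Management says: "Before surgery, a compliance diary will be provided to patients to evaluate their adherence". Administration says that "patients will fill out a daily compliance diary from the date of randomization until up to 5 days after surgery"; the diary is then transcribed to a preoperative case report form covering packets, volume, days and reasons for missing doses. For the time before admission, Administration also states: "The patients will be responsible for administering their own supplements while at home".

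The Blinding section gives the research pharmacy service (PReSS) a further duty: "PReSS will also be responsible for the accountability of the supplements throughout the study". No section links that duty to the compliance outcome.

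The result has two uses. Secondary Outcomes says compliance will be weighed when feasibility is judged and may lead to protocol changes. Statistical Analysis says reasons for noncompliance are explored only when compliance is below 70%.

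**The concern.** Most of the sachets behind the 41/58 cut are taken at home, unobserved, and enter the outcome on the patient's word. If some missed sachets are recorded as taken, the error goes one way: more patients cross the cut. The article names no check, although the pharmacy service already accounts for the supplements and patients come to hospital for their operation.

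What is at stake is the absolute level of compliance. An inflated level would make the regimen look more workable than it is, would switch off the analysis of why patients did not take it, and would carry into the design of the larger trial. Because participants are blinded, similar error in both arms is plausible. The between-arm description is therefore less exposed than the level itself.

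**Working it through.** **1. The plan's own figure.** 0.70 × 58 = 40.6, so the smallest whole number meeting the cut is 41 (41/58 = 70.7%; 40/58 = 69.0%). The stated cut is reproduced.

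**2. Where the 58 sachets fall.** From the sections on the three products:
- INergy-FLD: "Patients will be asked to consume 3 doses per day for 5 days prior to surgery and 5 days following surgery", so 3 × 5 = 15 before and 15 after.
- PreCovery: 2 + 1 = 3, all before surgery.
- ISOlution: one per day, all before surgery. The total implies 58 − 30 − 3 = 25, which matches day −30 to day −6.

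Preoperative: 25 + 15 + 3 = 43; 43/58 = 74%. Postoperative: 15.

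**3. Dependence on lead time.** The section on supplements and placebo says surgery should occur within 4 weeks of enrollment, so 30 days is the upper end. For a lead of L days (L ≥ 6), ISOlution sachets = L − 5, preoperative sachets = L + 13 and total = L + 28.

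| Lead (days) | Preoperative / total | Diary share | Diary alone can reach 41 (58 fixed) | 70% cut if scaled to days available | Diary alone can reach scaled cut |
|---|---|---|---|---|---|
| 30 | 43/58 | 74% | yes | 41 | yes |
| 28 | 41/56 | 73% | only if every sachet is recorded | 40 | yes |
| 27 | 40/55 | 73% | no | 39 | yes |
| 22 | 35/50 | 70% | no | 35 | only if every sachet is recorded |
| 21 | 34/49 | 69% | no | 35 | no |
| 14 | 27/42 | 64% | no | 30 | no |

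With a full 30-day kit and all 15 postoperative sachets charted by nurses, 41 − 15 = 26 sachets must still come from the diary.

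**4. What a recorded 41/58 could mean.** Assume the diary exceeds true preoperative intake by a fraction o, with p postoperative sachets taken. True total = (41 − p)/(1 + o) + p.
- o = 0.10, p = 15: 26/1.10 + 15 = 38.6, or 67% of 58.
- o = 0.20, p = 0: 41/1.20 = 34.2, or 59% of 58.

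For o from 10% to 20% and p from 0 to 15, true intake is about 59% to 67%.

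**5. Effect on the proportion classed as compliant.** Simulation of 400,000 patients: each patient's intake probability is drawn from a beta distribution, sachets are binomial, the full 43 + 15 are available, and a share of missed preoperative sachets is recorded as taken. Means, SDs and over-reporting shares are all assumptions.

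| True mean intake (SD) | Truly ≥41/58 | Reported, 10% of missed ticked | 20% | 30% |
|---|---|---|---|---|
| 40% (20) | 9.5% | 12% | 14% | 18% |
| 60% (20) | 36% | 40% | 45% | 51% |
| 65% (20) | 46% | 50% | 55% | 60% |
| 85% (15) | 84% | 86% | 88% | 91% |
| 90% (10) | 94% | 95% | 96% | 97% |

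With the denominator scaled to days available, 65% mean, SD 20 and 20% over-reporting, the rise is about 7 to 9 points at leads of 14 to 28 days. A shorter lead reduces the effect but does not remove it.

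**The case against.** - **Self-report alone.** A reader might infer that patients can generally meet 41/58 without one observed sachet. The documents do not support that. With 58 fixed it needs a lead of at least 28 days, at the edge of the 4-week window, and at 28 days every preoperative sachet must be recorded. If the last PreCovery serving is witnessed in hospital, 42 unobserved sachets remain at 30 days and 40 at 28 days.
- **Likely overstated.** A reader might also infer that compliance will probably be too high. The article gives no over-reporting rate, and blank diary days could push the figure down. The diary is also more than a tick-box, since volumes, days and reasons are recorded. Only the direction of effect, if over-reporting occurs, can be stated.
- **Limited consequence.** The go, modify or stop rule uses only the proportion randomized. Reasons for noncompliance are still recorded on the forms; only their exploratory analysis is conditional. This stands and limits the weight of the point.
- **Silence in an article.** Return and count procedures may be in the full protocol or a pharmacy manual. This stands for the procedures. It does not answer the point that three sections state the preoperative source of the outcome and none includes a count.
- **Limits of a count.** It cannot measure volume, treats discarded sachets as taken, and would come from staff who know the allocation. Always taking the lower of diary and count would build in a downward rule. So the count should stand beside the diary, not replace it.

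**Conclusion.** The concern holds as a weakness in a stated measurement choice, not as an arithmetical error or contradiction. Between about 64% (14-day lead) and 74% (30-day lead) of the available sachets rest on an unverified diary, while an accountability role that could check it already exists.

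If over-reporting occurs, it raises the absolute proportion classed as compliant. Its size is unknown. Under the assumed 10% to 30% over-reporting, the rise is about 4 to 15 points when mean true intake is 60% to 65%, and about 1 to 9 points at the means further from the cut. The effect is largest when many patients truly lie near or just under 70%. These figures assume the full 30-day kit and the intake distributions shown.

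The primary outcome is untouched, and the comparison between blinded arms is less exposed. This is a worthwhile low-cost improvement rather than a fault that threatens the trial.

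**What to change.** In Administration and Secondary Outcomes:

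1. Ask patients to bring unused and empty preoperative sachets to the surgical admission.
2. Have the pharmacy service count them under its existing accountability role and pass on only the count, so that research staff stay blinded. Reconcile the count with the diary.
3. Keep the diary as the source for partial volumes, dates and reasons.
4. Report the proportion compliant twice: from the diary, and from the count (sachets dispensed for the days available minus those returned unopened). Postoperative intake stays as charted by nurses in both. State how many kits were not returned.
5. Explore reasons for noncompliance if either source shows less than 70%.

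The cost is one line in the patient instructions, one field on the preoperative compliance form and a few minutes of counting per patient. The downsides are that some kits will not come back, discarded sachets escape the count, and the compliance figure may look less favourable.

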### Adjudication

An adjudication committee consisting of 2 experts in the field will review each patient’s complications using deidentified source documents including discharge summaries, operative reports, interventional radiology reports, imaging reports, microbiology reports, and physician hospital and clinic progress notes as well as consultation notes from other physicians. The first adjudicator will review each complication, confirming that all reported complications are accurate, not duplicated, and appropriately classified. Whenever there is agreement with the site-reported outcome, then the outcome is considered confirmed. If there is a disagreement between the site and the first adjudicator, the second adjudicator will review that particular file. Any disagreement will be resolved by consensus, either by agreeing with the site or with the first adjudicator. Variables recorded include the length of hospital stay, blood work results, microbiology data, operating room time, estimated blood loss, number of blood transfusions during surgery and the hospital stay, and reoperations or readmissions. Each complication must be supported by source documents. The outcome assessment will follow the strict criteria set by Clavien-Dindo classification [26,31,35] and the CCI [26,31]. The outcome assessors will undergo adjudication training.

### Adverse Events

The study will be conducted according to the International Conference of Harmonization and Good Clinical Practice consolidated guidelines. Currently, there are no foreseeable risks in administering nutritional supplements to patients who meet the eligibility criteria. Nutritional supplements are safe when used by adults as instructed [36,37].

**Table 1 table1:** The study timeline.

Planned completion date	Study goals
December 2017-September 2018	Attain Initial Research Ethics Board Approval, receive initial shipment of the Nutritional Supplements and Placebo, and submit Research Ethics Board Amendments for approval required prior to recruitment
October 2018	Begin recruiting patients
July 2018	Have 50.0% (50/100) of participants enrolled in the study
April 2020	Complete study enrollment. Have 100% (100/100) of participants enrolled in the study
May-September 2020	Complete final follow-up visits
October-December 2020	Complete final statistical analysis and begin preparing manuscript
December 2020	Have final manuscript completed and ready for publication

If an adverse event (AE) occurs during the study and is deemed related to the administration of the study treatment, this will be reported using version 4.0 of the Common Terminology Criteria for Adverse Events (Multimedia Appendix 2) [38]. This data will be collected from the first administration of treatment until the last study visit.

The investigational food products are ISOlution (whey protein isolate), INergy-FLD (immunonutrition), and PreCovery (carbohydrate loading). AEs will be considered related to study product if they are deemed to be related specifically to the administration of ISOlution, INergy-FLD, or PreCovery.

Worsening of gastrointestinal cancer is expected and therefore will not be considered an AE for the purpose of this study. Deaths due to gastrointestinal cancer are outcome events and will not be reported as AEs.

### Scientific Reporting and Publication

The Steering Committee is responsible for the scientific reporting, publishing, and presentation of the study results. All investigators participating in this study must agree to delegate the primary publication or presentation responsibility to the Steering Committee. Any other publication or presentation related to the study and the results by any investigator or participant must receive prior approval from the Steering Committee. No other publication or presentation is allowed before the primary publication or presentation by the Steering Committee. Authorship will be determined by the Steering Committee. The information developed during the conduct of this study is considered confidential.

The timeline for the study can be found in Table 1. We obtained research ethics approval from our local REB in December 2017. We aim to recruit 50 (100) patients of the patients by July 2019. The estimated study completion date is December 2020.

